### Setting

PhysioDirect services will be newly established in four areas of England. Each physiotherapy service will provide care for patients from a defined group of practices within one of the following Primary Care Trusts (PCTs): Bristol, Somerset, Stoke-on-Trent, Central and Eastern Cheshire PCT. The total population covered across all four PCTs will be about 625,000 people. The existing physiotherapy services received about 18,300 referrals from primary care professionals in these practices in 2008.

### Participants

The inclusion criteria are as broad as possible in order to maximise generalisability and to reflect the 'real-world' operation of PhysioDirect services. Inclusion criteria are adults (aged 18 years or over) who are referred by GPs or other members of the primary health care team, or who refer themselves (self-referred) for musculoskeletal physiotherapy.

Exclusion criteria are children (< 18 years); patients referred to physiotherapy by a hospital consultant, emergency department or primary/secondary care interface service; those needing domiciliary physiotherapy; those needing post-operative physiotherapy; those needing physiotherapy for non-musculoskeletal problems; those unable to communicate by telephone in English.

GPs or health care professionals in the relevant practices will refer patients to physiotherapy in their usual way, or patients may refer themselves. Referral forms will be screened by a senior physiotherapist within one working day to confirm that the patient is potentially eligible, and eligible patients will be sent information about the trial by post, along with a consent form and a baseline questionnaire. Patients who give consent to participate and complete the baseline questionnaires will be randomised in a 2:1 ratio to PhysioDirect or usual care. This allocation ratio was chosen to ensure that sufficient people are randomised to PhysioDirect to make it viable to establish this new service, given that non-consenting and excluded patients will continue to receive usual care as well as those randomised to usual care. Randomisation will be undertaken using web or telephone access to a secure remote allocation system, with allocation made at the level of the individual, minimising by PCT, gender, patient age group and presenting complaint. Following randomisation, patients will be sent a letter either inviting them to contact PhysioDirect and telling them how to do so (intervention arm), or telling them that they are on a waiting list for a face-to-face appointment (control arm).

The number of patients excluded from the trial for different reasons will be recorded. The age and sex of all patients will be recorded in anonymised form, to make it possible to compare participating and non-participating populations. Eligible patients who decline to participate will receive usual care.

### Description of intervention and control arms

#### Intervention

'PhysioDirect'. As soon as possible after consent to participate in the trial is received the patient will be invited to telephone a senior physiotherapist for initial assessment and advice. The physiotherapist will follow a computerised algorithm (as developed by the PhysioDirect service in Huntingdonshire) to assess the patient and record findings. In most cases, at the end of the consultation the physiotherapist will post a relevant advice leaflet about self-management and exercises to the patient, inviting them to phone back to report progress after about 2 to 4 weeks if appropriate. At that point they can be given further advice or be booked for a face-to-face consultation if necessary. Alternatively, the initial phone call may establish that more urgent face-to-face care is needed, in which case this will be booked at the outset, or the assessment may establish that physiotherapy is unlikely to be effective and the patient can be given appropriate advice and discharged. In this way those patients most likely to benefit from face-to-face physiotherapy should be able to receive it more quickly, hopefully leading to a faster improvement and a quicker return to work and usual activities.

All four physiotherapy services participating in this trial will set up a PhysioDirect service following the same model of organisation and using the same assessment software, as developed in Huntingdonshire. All physiotherapists operating the PhysioDirect services will undertake a structured training programme and be assessed and certified as competent to undertake PhysioDirect before they assess patients in the trial. Training and assessment of competency will be undertaken by PhysioDirect trainers from Huntingdon PCT. In this way, we will seek to ensure consistency in the way the intervention is developed in each service. Each PhysioDirect service will have a run-in period of at least two months to ensure smooth running of the service before patients to be included in the trial are recruited.

#### Control

Usual care involves patients being referred by a GP or other member of the primary health care team to a physiotherapist. In some areas, patients may also refer themselves directly. Patients go onto a waiting list for an initial face-to-face physiotherapy assessment and then usually have a series of follow-up treatment appointments for several weeks or months. The waiting time may differ considerably at different services, at different sites providing physiotherapy within one service, and at different times of year.

### Outcome assessment

Outcomes will be assessed at baseline, and at 6 weeks and 6 months after randomisation.

The primary outcome is clinical outcome at 6 months, assessed using the physical component summary (PCS) measure from the SF-36v2 questionnaire [28]. The SF-36v2 PCS is a well recognised generic measure of health status. It is particularly suitable for this trial because, unlike disease specific measures, it is applicable to the wide range of musculoskeletal problems referred to physiotherapy.

Two further measures of clinical outcome will be used and considered as important secondary outcomes. The first is the MYMOP2 [29] questionnaire, which is a patient generated measure. It allows patients to specify up to two symptoms and one functional limitation for which they have been referred to physiotherapy, and follow-up questionnaires assess change in those specific symptoms/limitations. This individualised and validated measure can also be used by patients with a wide range of problems [29]. Secondly, a single question will be included as a global measure of individual perception of overall improvement (based on a seven point Likert scale from 'very much worse' to 'very much better'). This type of global improvement score is recommended by the Outcomes Measures in Rheumatology Clinical Trials- Osteoarthritis Research Society International (OMERACT-OARSI) initiative [30].

Other secondary outcomes are:

• costs

• quality of life (measured using the EQ5D measure [31]

• the individual scales and the mental component summary measure from the SF-36

• waiting times for treatment

• time lost from work and usual activities

• satisfaction with care provided

• preference for telephone or face-to-face assessment.

### Collection of data

The baseline questionnaire will collect data about patient characteristics and about the outcome measures. Data about outcomes at follow-up will be collected from postal questionnaires sent at 6 weeks and 6 months after randomisation. Data will be collected by telephone instead of post where patients do not respond to a postal questionnaire or a postal reminder, where patients express a preference for telephone administration, or where patients are unable to complete written questionnaires in English. Data about use of healthcare resources will be extracted from physiotherapy service records and medical records, and details of use of other resources will come from the patient questionnaires.

Table 1 lists the various outcome measures, the timing of data collection and the source of the data.

**Table 1 T1:** Outcome measures, timing of data collection and source of data

	**Timing**	**Source**
Patient identifiers, type of problem, age and sex	Pre-consent	Referral letter. Recorded (anonymised) in research database

Demographic details	Baseline	Baseline patient questionnaire

SF36v2	Baseline, 6 weeks, 6 months	Patient questionnaires

MYMOP	Baseline, 6 weeks, 6 months	Patient questionnaires

EQ5D	Baseline, 6 weeks, 6 months	Patient questionnaires

Overall perception of improvement	6 weeks, 6 months	Patient questionnaires

Time lost from work and usual activities	Baseline, 6 weeks, 6 months	Patient questionnaires

Satisfaction with care provided	6 weeks, 6 months	Patient questionnaire

Preference for Physiodirect or usual care	Baseline, 6 months	Patient questionnaires

Waiting time for treatment	Collected at end of study	Physiotherapy service records, from date of referral received to date first phone or face-to-face consultation

Patient and companion costs	6 weeks, 6 months	Patient questionnaires

Cost of lost production associated with time off work and usual activities.	6 weeks, 6 months	Estimated from information in patient questionnaires

Costs of providing physiotherapy	Set up costs: collected during set up phase and once the service is operating. Treatment over 6 months: collected at end of study.	Set up: data from PCTs about resources involved in setting up the service; Treatment: physiotherapy records, data collected within the trial about lengths of consultations, staff use of time, staff grades etc.

Costs in general practice (consultations, treatments, investigations)	Collected at end of study, from randomisation to 6 months	Patients GP records, consultations costed using Netten and Curtis and NHS reference costs for other costs

Costs of prescriptions	Collected at end of study, from randomisation to 6 months	Patients GP records, costed using British National Formulary

NHS secondary care costs (outpatients, inpatients, admissions)	6 weeks, 6 months	Patient questionnaires for resource use, costed using NHS tariffs

Process evaluation: number, type & duration of consultations with physiotherapists; non-attended appointments with physiotherapists.	Collected throughout study from randomisation to 6 months	Physiotherapy records

Qualifications and experience of physiotherapists.	Collected at the beginning of the study	Online questionnaire completed by physiotherapists

Complaints and adverse events	Collected throughout study from randomisation to 6 months	Notified by patients, physiotherapy services, general practices or any other sources.

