## Abstract

**Background:**

Providing timely access to physiotherapy has long been a problem for the National Health Service in the United Kingdom. In an attempt to improve access some physiotherapy services have introduced a new treatment pathway known as PhysioDirect. Physiotherapists offer initial assessment and advice by telephone, supported by computerised algorithms, and patients are sent written self-management and exercise advice by post. They are invited for face-to-face treatment only when necessary. Although several such services have been developed, there is no robust evidence regarding clinical and cost-effectiveness, nor the acceptability of PhysioDirect.

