### Existing evidence about PhysioDirect

Local evaluations and one small trial of PhysioDirect suggest that services based on telephone advice given by physiotherapists are likely to be popular with patients [25], although there is no evidence about costs or outcomes, or the important issue of safety. Audits in the pioneering services in Cheltenham and Huntingdonshire suggested that 40–60% of patients referred by GPs to physiotherapy can be managed by telephone alone without a face-to-face consultation, telephone consultations take approximately half as long as face-to-face consultations, waiting times for a face-to-face appointment were reduced from four weeks to 10 days and 'did-not-attend' (DNA) appointment rates were reduced from 15% to 1%. Patients were very satisfied with the service, with 80% rating it as good or excellent [25-27]. These findings demonstrate the potential benefits of PhysioDirect, but the lack of comparative data from concurrent controls, and a lack of robust data about clinical outcomes and costs, means that there is insufficient evidence currently available to justify the widespread implementation of this new way of working.

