### Process evaluation

Process data about the physiotherapy services provided will include: the number, type and duration of consultations with physiotherapists; rates of non-attended appointments with physiotherapists; and the qualifications and experience of all the physiotherapists involved at all four sites. Complaints and adverse events relating to the physiotherapy services will be systematically recorded and investigated.

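### Adverse events are found only by notification while physiotherapy contact differs between arms by design, so ascertainment may differ by arm, in an uncertain direction

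*Protocol article*

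**What the plan says.** The adverse-event row of Table 1 (Collection of data) gives the timing as "Collected throughout study from randomisation to 6 months" and the source as "Notified by patients, physiotherapy services, general practices or any other sources". The Process evaluation section adds that "Complaints and adverse events relating to the physiotherapy services will be systematically recorded and investigated".

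The questionnaires at 6 weeks and 6 months go to both arms, but Table 1 does not list adverse events among their contents. General-practice records and patient-reported hospital use are also gathered in both arms, and both are listed for costing.

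On contact, the Abstract says of PhysioDirect patients: "They are invited for face-to-face treatment only when necessary". The Intervention section has the physiotherapist post a leaflet in most cases, "inviting them to phone back to report progress after about 2 to 4 weeks if appropriate". Under Control, usual-care patients join a waiting list, are then assessed in person, and usually return for further visits. The section on existing evidence reports audits of earlier services in which "40–60% of patients referred by GPs to physiotherapy can be managed by telephone alone without a face-to-face consultation". The same section says evidence is lacking on costs and outcomes, "or the important issue of safety".

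**The concern.** Under notification, an event enters the data only when somebody reports it. If the opportunities to report differ between arms, the recorded counts mix the true event rate with the chance of detection, and the two cannot be separated afterwards.

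That matters here because the document names safety as an evidence gap and promises evidence to inform decisions on NHS implementation. Readers will set the event counts of the two arms side by side even though no formal test is planned. No analysis plan can repair the problem later: a question that was not put to patients at 6 weeks and 6 months leaves no answer to analyse.

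**Working it through.** **Is this a stated method or a gap?** It is stated. The other patient-level follow-up rows of Table 1 name a questionnaire or a record source applied to both arms. The adverse-event row names notifiers. The Process evaluation sentence says what is done with events relating to the physiotherapy services once they are known. It does not say how unreported events are sought. An event diagnosed elsewhere and not linked to the service could fall outside it.

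**Which routes depend on the arm?**
- Physiotherapy service: yes. PhysioDirect contact starts early, by telephone, and may end there. Usual-care contact starts later, is in person, and usually recurs.
- Patients, general practices and other sources: open to both arms.

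**Size.** The document gives no event rate, detection rate or safety precision, so there is no figure of its own to reproduce. What follows is illustration.

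Inputs:
- *f*, the share managed by telephone alone: 0.4 to 0.6, from the audits of earlier services, not from this trial.
- *s*, detection without the relevant contact relative to detection with it: assumed.
- *w*, the share of the 26-week window that a usual-care patient spends waiting: 4/26 = 0.154 to 12/26 = 0.462. The waits of 4 and 12 weeks are assumed. For comparison, the article cites four weeks before one service changed, and several months in some areas.
- True rate ratio: 1.

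*Scenario A: detection is lower in patients managed by telephone only.* Apparent ratio (PhysioDirect / usual care) = 1 − f(1 − s).

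| s | f = 0.4 | f = 0.6 |
|---|---|---|
| 1 | 1.00 | 1.00 |
| 0.9 | 0.96 | 0.94 |
| 0.75 | 0.90 | 0.85 |
| 0.5 | 0.80 | 0.70 |

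For example, 1 − 0.6 × 0.5 = 0.70.

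*Scenario B: telephone contact detects as well as face-to-face contact, and detection is lower while usual-care patients wait.* Apparent ratio = 1 / [1 − w(1 − s)].

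| s | w = 4/26 | w = 12/26 |
|---|---|---|
| 0.9 | 1.02 | 1.05 |
| 0.75 | 1.04 | 1.13 |
| 0.5 | 1.08 | 1.30 |

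For example, 1 / (1 − 0.462 × 0.5) = 1 / 0.769 = 1.30.

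*Both at once, s = 0.5.* With f = 0.6 and w = 4/26: 0.70 / 0.923 = 0.76. With f = 0.4 and w = 12/26: 0.80 / 0.769 = 1.04. The two mechanisms can partly or wholly offset each other.

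The span of about 0.7 to 1.3 therefore belongs to s = 0.5. Values of s nearer 1 shrink it. At s = 0.25 it widens to 0.55 (A, f = 0.6) and 1.53 (B, w = 12/26).

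**The case against.** The strongest reply has four parts.

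*This is a condensed article.* How events are solicited commonly sits in the full protocol, which is not shown, and the text does promise systematic recording. This stands in part. If the full protocol already contains an active enquiry in both arms, the point reduces to correcting the Table 1 row. As published, though, the row states notification, and recording what is notified differs from asking.

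*The direction is not established.* A reader might infer that events will be missed mainly under PhysioDirect and that the service will look safer than it is. The documents do not support this. PhysioDirect patients are contacted earlier and may call back. Usual-care patients wait longer on average. Patient and GP notification need no physiotherapy visit, and a problem missed by telephone could well surface with the GP or at hospital. More hands-on treatment could also cause more genuine events, so a lower PhysioDirect count could be partly real. Nor are all usual-care patients seen: the Background says many fail to attend. This part stands in full.

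*No safety comparison is planned.* Safety is not a research question, a listed outcome or a stated analysis; adverse events sit under process evaluation. This also stands, and limits the consequence to a descriptive conclusion.

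*Data that do not rest on notification exist.* GP consultations, hospital use including A&E visits, and the global change item are collected in both arms. This is true, so a notified-event result would not be wholly unreadable. But those data are assigned to costs and outcomes, and nothing in the article directs them to adverse events.

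**Conclusion.** The point holds in a limited form. The stated ascertainment rests on notification, and one of the named routes differs between arms by design, so the recorded event counts are open to differential detection.

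The size cannot be derived from the document. At an assumed relative detection of one half, equal true rates could appear as a ratio from about 0.7 to about 1.3. With no detection deficit there is no bias. A reader might take the low end alone and conclude that a true PhysioDirect excess of 25% to 43% would be hidden (1/0.80 = 1.25, 1/0.70 = 1.43). That figure needs both the assumed halving and the absence of any waiting-list effect, and the documents support neither.

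The primary SF-36 comparison is unaffected. What is weakened is any descriptive statement that the two pathways are similarly safe.

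**What to change.** 1. Add one short adverse-event question, worded identically for both arms, to the existing 6-week and 6-month questionnaires. It should not ask the patient to attribute the event to physiotherapy; judge relatedness afterwards by the same rule in both arms.
2. During the GP-record extraction already planned (randomisation to 6 months), and using the hospital-use data already collected, check both arms against one fixed list for new serious diagnoses or emergency contacts linked to the referred problem. The record check does not depend on questionnaire return, which matters because the sample-size section allows for 20% non-collection.
3. Keep the notification route. Report events by arm with confidence intervals and by route of detection, so that actively sought and notified events can be read separately.
4. Amend the Table 1 row to name these sources.

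The cost is a slightly longer questionnaire, a few more extraction fields and more minor events to review. The questionnaires and record extraction are already planned. The change has to be made before follow-up questionnaires go out, because the missing answers cannot be recovered at analysis.

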### Economic evaluation

The economic evaluation will be carried out from three perspectives. Costs to the NHS will include the cost of providing physiotherapy plus any other costs related to treating the condition for which the patient has been referred to the physiotherapy service. These include: primary care consultations, treatments and investigations, medication, secondary care consultations, and inpatient care. Set-up costs associated with the service will also be collected. Patient and companion costs will include: travel, dependent carer costs, private treatment, over-the-counter medication, and loss of earnings. Societal costs will include use of social services, disability payments, and time off work.

Data will be obtained from four main sources: the patient self-completion questionnaires at baseline, 6 weeks and 6 months after randomisation; primary care patient records; patient records at the physiotherapy services; and records kept as part of the trial detailing length of consultation, grade of staff, and amount of non-contact time. A time and motion study will be conducted to observe activities during non-contact time to estimate the opportunity cost of that time.

Curtis [32] will be used to value primary and community care consultations. Primary care investigations will be valued at cost; the Department of Health tariff will be used for A&E visits, out-patient visits and investigations, and inpatient stays; and the British National Formulary will be used to cost prescribed medication. Most patient and carer costs will be directly reported; the AA schedule for valuing mileage will be used to cost car journeys Time off work by patients and carers will be valued using patient-level information on how absenteeism is dealt with by employers, and will adopt the friction approach, which includes only the resources required to replace the employee [33]. There will be no need to discount costs or outcomes, as they will cover a period of less than one year.

### Process evaluation

Process data about the physiotherapy services provided will include: the number, type and duration of consultations with physiotherapists; rates of non-attended appointments with physiotherapists; and the qualifications and experience of all the physiotherapists involved at all four sites. Complaints and adverse events relating to the physiotherapy services will be systematically recorded and investigated.

### Qualitative research

Qualitative research will be conducted alongside the trial to study issues of implementation and to understand the key barriers and facilitators to the success of a PhysioDirect service. The qualitative research will also examine the acceptability of the service and identify the factors (organisational, professional and patient related) which influence its implementation. The interviews will be conducted in person or by telephone and longitudinal data collection will allow themes to be followed up with participants over time.

Interviews will be carried out with a purposive sample of 40–60 patients to explore the accessibility of the service, the value, acceptability and influence of telephone and face-to-face care, and how services could be improved. Participants in the interviews will be selected to ensure a diverse sample based on age, gender, ethnicity and presenting clinical problem in order to get the widest range of opinions and experiences.

Interviews with a purposive sample of between 20–30 key informants (physiotherapists, GPs, practice-based commissioning leads and managers) will address contextual factors that act to facilitate or hinder the use and implementation of PhysioDirect or usual physiotherapy services, or that influence outcomes, and the perceived value of the services.

